### Statistics

#### General considerations

As noted above, the safety of cellular therapy administration in the first five patients will be reviewed by the Data Safety Monitoring Board. These reviews will be shared with our institutional IRB. If the treatment appears safe, as determined by the Data Safety Monitoring Board with institutional IRB agreement, the protocol may be reopened to treat a total of 20 patients.

For statistical analysis of efficacy endpoints, descriptive statistics are computed for variables of interest (mean and SD for continuous variables and frequencies for categorical variables). Test results are summarized over time using appropriate graphical or tabular formats. The non parametric pair wise Wilcoxon rank sum test will be used to investigate each variable within subject and between the same subject at different follow-up (e.g. pre- vs. post-MSC, pre- vs. post-sham, etc.). The use of a non-parametric test has been considered the most appropriate since the distribution of the variable is not known and the number of observations is relatively small. For each time point, the test will be performed with 20 paired values (the values before and after MSC therapy in the 10 subjects allocated to immediate treatment plus the 10 subjects allocated to the delayed treatment).

P-values < 0,05 will be considered statistically significant. Additional summary statistics are also considered as appropriate to the data.

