#### Multifactorial movement analysis

The data related to each of the four tests will be normalized and the mean of the values related to each variable recorded during the 8 walks will be calculated. The data before and after MSC therapy will be compared using Wilcoxon’s signed rank test for matched pairs, considering the patients before and after treatment as a pair (the results at each follow-up visit will be assessed separately). Moreover, the results obtained in PSP patients will be compared with those obtained in the group of age-matched healthy volunteers using the non-parametric Mann–Whitney U Test.

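### The general efficacy rule names an independent-samples test (Wilcoxon rank sum) for 20 before/after pairs, while the movement-analysis section names the signed rank test for the same kind of comparison

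*Protocol article*

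**What the plan says.** The general efficacy rule is in the protocol article under Statistics, General considerations. It reads: "The non parametric pair wise Wilcoxon rank sum test will be used to investigate each variable within subject". The sentence goes on to describe what is compared: "between the same subject at different follow-up (e.g. pre- vs. post-MSC, pre- vs. post-sham, etc". The number of observations is also given as pairs: "For each time point, the test will be performed with 20 paired values", made up of 10 patients allocated to immediate and 10 to delayed treatment. The significance threshold in the same section is "P-values < 0,05 will be considered statistically significant".

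The statistical section on multifactorial movement analysis covers the same kind of comparison with a different test: "The data before and after MSC therapy will be compared using Wilcoxon’s signed rank test for matched pairs". It uses the independent-samples test only where the groups really are independent, to compare patients with a "group of age-matched healthy volunteers using the non-parametric Mann–Whitney U Test".

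The statistical sections on motor function and on neuropsychological assessments promise descriptive analyses and name no test. The neuroimaging section names ANOVA.

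**The concern.** The Wilcoxon rank sum test is the Mann–Whitney test. It ranks all values from two independent groups together and has no matched-pair form. Used on before and after values of the same patients, it ignores the pairing and takes the spread between patients as its error. When a patient's two scores are positively correlated, that error is too large for the comparison being made, so the test rejects too rarely and loses power.

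The general rule covers each efficacy variable, and it is the only place that names a test for the motor and neuropsychological endpoints. An analyst must choose between the name of the test and the description of its use, and the two can lead to different conclusions from the same data. That choice should not be open once data are in hand.

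**Working it through.** **1. The two statements side by side.**

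| | General considerations | Movement analysis |
|---|---|---|
| Data | same patient, before vs after | same patient, before vs after |
| Unit counted | 20 pairs | the patient before and after, as a pair |
| Test named | Wilcoxon rank sum | Wilcoxon signed rank, matched pairs |
| Independent-samples test | the same rank sum test | Mann–Whitney U, patients vs volunteers only |

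The data structure is the same and the named tests differ. Only the signed rank test fits paired data.

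**2. Is there a figure to reproduce?** No. The article gives no power, effect size, SD or within-patient correlation, so the effect of the name can only be shown under assumptions.

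**3. Inputs.** From the article: 20 pairs and a 0.05 threshold. Assumed: a two-sided test (sidedness is not stated), bivariate normal scores, a within-patient correlation ρ from 0 to 0.8, and a true shift of 0.5 SD of the raw score.

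**4. Analytic approximation for type I error.** For a difference of two means from n pairs, the true variance is 2σ²(1−ρ)/n, while an unpaired test assumes 2σ²/n. The ratio is 1−ρ, so the actual type I error is about 2·[1 − Φ(1.96/√(1−ρ))].

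- ρ = 0: 1.96/1 = 1.96, giving 5.0%
- ρ = 0.3: 1.96/0.837 = 2.34, giving 1.9%
- ρ = 0.5: 1.96/0.707 = 2.77, giving 0.56%
- ρ = 0.7: 1.96/0.548 = 3.58, giving 0.035%

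This is a formula for means and so only a rough guide for ranks.

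**5. Simulation.** 40,000 trials per setting with 20 pairs each. The rank sum test used the asymptotic form with continuity correction. The signed rank test used its exact critical value, W ≤ 52, for which the exact two-sided type I error is 4.84%.

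| ρ (assumed) | Type I error: rank sum | Type I error: signed rank | Power at 0.5 SD: rank sum | Power at 0.5 SD: signed rank |
|---|---|---|---|---|
| 0 | 5.0% | 5.0% | 32% | 31% |
| 0.3 | 2.1% | 4.7% | 30% | 42% |
| 0.5 | 0.8% | 4.7% | 27% | 55% |
| 0.7 | 0.1% | 4.9% | 24% | 76% |
| 0.8 | 0.02% | 5.0% | 22% | 91% |

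The simulation shows the same pattern as the approximation. The rank sum test loses nothing at ρ = 0, a moderate amount at 0.3, about half the power at 0.5 (27% against 55%), and more above that. The signed rank test stays close to its nominal level throughout.

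**The case against.** The strongest reply is that this is a slip of terminology and not a plan to run an unpaired test. The sentence itself calls the test pairwise and within-subject, the paragraph counts paired values, and the movement-analysis section shows that the authors know both tests and keep the Mann–Whitney test for independent groups. On that reading the test actually run has a type I error of about 4.8% and no power is lost. This stands as to intent, and it limits the harm. It does not make the text correct: the general rule still names the wrong test, and nothing in the article says which of name and description governs.

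Three further limits also stand.

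- The size of any loss depends on a correlation that the article does not give. It also rests on a normal model, which represents coarse ordinal measures such as Hoehn and Yahr stage or CGI poorly.
- A reader might infer that this is the trial's main efficacy test. The article does not say so: safety is the primary objective, efficacy is secondary, and no primary efficacy endpoint or test is named.
- A reader might also infer that a missed deterioration would be reported as stabilization. Stabilization is listed among the efficacy aims, but nothing says that a non-significant result will be read that way.

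**Conclusion.** The point holds as an error of naming and an internal inconsistency. The general efficacy rule specifies an independent-samples test for 20 within-patient pairs, against the test that the article itself names for the same kind of comparison in movement analysis. The signed rank test was probably intended.

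The tempting stronger statement, that the efficacy analysis is far too conservative, is not supported. It would be true only if the rank sum test were run literally and the within-patient correlation were clearly positive. Under those conditions the loss is real and can be large, as the table shows. With zero correlation, or with the signed rank test, there is none. Those figures rest on assumed correlations, a two-sided test, normal scores and a 0.5 SD shift.

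**What to change.** In Statistics, General considerations, replace the pairwise Wilcoxon rank sum test with the Wilcoxon "signed rank test for matched pairs" for all within-patient comparisons (before/after MSC, before/after sham, and between follow-up visits), in line with the movement-analysis section. This changes one phrase. It affects neither the design, the sample size nor the data collected. If the signed rank test was always intended, the text will simply say so. Whether the two randomized arms should also be compared is a separate question that this correction does not touch.

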**Discussion:**

To our knowledge, this is the first clinical trial to be applied in a no-option parkinsonism that aims to test the safety and to exploit the properties of autologous mesenchymal stem cells in reducing disease progression. The study has been designed to test the safety of this “first-in-man” approach and to preliminarily explore its efficacy by excluding the placebo effect.

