### Primary and secondary objectives

The primary objective is to assess the safety of autologous MSC therapy in patients with PSP in a “first-in-man” context.

The secondary objective is to assess the efficacy of autologous MSC therapy in patients with PSP in terms of stabilization or improvements in motor function, neuropsychological parameters and neuroimaging findings.

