In this study a “pure” control group treated with placebo solution administered by the same route in a double-blinded manner is missing since this option was considered not acceptable by the ethical point of view by the investigators, given the potential harm of a cerebral artery catheterization procedure that is not justified by a potential benefit. Nevertheless, the patients enrolled in the control harm receive a simulated arterial catheterization and administration procedure and the neurologist and the neuro-radiologist who perform the follow-up evaluation are blinded. In this way, we exclude the placebo effect with the best precision.

In conclusions, the presented protocol is the first attempt to understand if MSC can be safely administered and can exert a beneficial effect in PSP patients. We believe that the results of this trial will help to improve the knowledge around the neuroprotective properties of MSC that might be exploited in other several neurodegenerative disorders.

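### The stated efficacy test pools before/after-MSC pairs from both randomised arms, and no stated test compares MSC with sham, so the secondary efficacy objective lacks a controlled analysis

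*Protocol article*

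**What the plan says.** Under Study design, patients in the randomised phase receive either MSC first and sham later, or sham first and MSC later, with 6 months between the procedures.

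Under Statistics, General considerations, each variable is tested "within subject and between the same subject at different follow-up (e.g. pre- vs. post-MSC, pre- vs. post-sham, etc". The sample for this test is then fixed: "For each time point, the test will be performed with 20 paired values", namely "the values before and after MSC therapy in the 10 subjects allocated to immediate treatment plus the 10 subjects allocated to the delayed treatment". The threshold is also given: "P-values < 0,05 will be considered statistically significant".

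The endpoint sections do not add a comparison of the arms:
- Motor function and Neuropsychological assessments promise descriptive summaries.
- Multifactorial movement analysis tests before against after MSC. Its only two-group test is PSP patients against healthy volunteers.
- Neuroimaging assessment names an ANOVA of changes but no factors.

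The efficacy objective is "stabilization or improvements in motor function, neuropsychological parameters and neuroimaging findings". The Abstract says the study is designed "to preliminarily explore its efficacy by excluding the placebo effect". The Discussion presents the sham control as the means of documenting efficacy, and says of the simulated procedure and blinded evaluation that "we exclude the placebo effect with the best precision".

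**The concern.** The reason for a sham arm is that the difference between MSC and sham removes whatever the two have in common: disease progression, expectation and repeated testing. Pooling both arms around the date of MSC removes that difference from the analysis. What remains is a single-group before/after test, even though the Discussion itself notes that improvement in earlier open-label studies could reflect the beliefs of patients and investigators.

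The null hypothesis is also badly matched to the objective. PSP is progressive, so zero change is what full stabilisation would predict. A product that truly slows decline can still show significant worsening after MSC, and a non-significant result may reflect only a small sample. Running a before/after-sham test alongside does not help, because two separate p-values do not test a difference.

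At stake is the secondary efficacy objective and the statements about the placebo effect.

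**Working it through.** **Stated figure.** 10 immediate + 10 delayed = 20 pairs, as the article says. It gives no effect size, SD, power or rate of decline, so there is no sample-size calculation to reproduce.

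**What each contrast estimates.** Let d be the natural change over the interval, p the placebo response and m the MSC effect.
- Before/after MSC: d + p + m
- Before/after sham, delayed arm, months 0 to 6: d + p
- Immediate MSC minus immediate sham over months 0 to 6: (d + p + m) − (d + p) = m

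Only the third isolates m, and it is not among the stated tests. In addition, in the delayed arm the pre-MSC value follows sham and 6 further months of disease, so the 20 pairs mix disease stages. In the immediate arm, sham comes 6 months after MSC, so its before/after change may still contain m. That leaves 10 clean sham pairs.

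**Simulation.** 4,000 trials per setting. Assumptions: normal change scores with SD 1, independent changes, the same decline in each interval, no dropout, two-sided 0.05. I took the paired test as Wilcoxon signed-rank, the name used under Multifactorial movement analysis. The between-arm test is exact Mann-Whitney, 10 versus 10. MSC is inert (m = 0).

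| Assumed decline (SD) | Pooled 20-pair test significant | MSC significant, sham (10 pairs) not | Sham significant, MSC not |
|---|---|---|---|
| 0.3 | about 22-24% | about 19-21% | about 10% |
| 0.5 | 54% | 39% | 13% |
| 0.7 | 83% | 42% | 9% |

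The between-arm test rejects in about 4-5% of trials for any assumed decline from 0 to 1 SD. A placebo improvement of the same size gives the same rates with the direction reversed, which would be read as benefit. The high third column arises partly because 20 pairs are set against 10.

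**When MSC works.** Suppose natural decline is 1 SD.
- MSC halves it: the pooled test is still significant, in the direction of worsening, in about 53-57% of trials.
- MSC stops it completely: the pooled test is significant in only about 5%, while the between-arm test detects the effect in about 51%.

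**Precision of the between-arm contrast.**
- 10 versus 10, 95% CI half-width: 2.101 × √(1/10 + 1/10) = 0.94 SD.
- 10 versus 10, 80% power, normal approximation: (1.96 + 0.84) × √(2/10) = 1.25 SD; with the t distribution, about 1.33 SD.
- If the total of 20 includes the 5 open-phase patients, 15 are randomised. For 7 versus 8: 2.80 × √(1/7 + 1/8) = 1.45 SD, or about 1.6 SD with the t distribution.

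**The case against.** This is a first-in-man phase I trial. Safety is primary, efficacy is exploratory, and most clinical endpoints are to be summarised descriptively. That stands, and it limits the point: neither the safety analysis nor the safety review after the first five patients depends on this test.

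Three stronger readings are tempting but unsupported.
- A reader might infer that the sham data go unused. They do not: a before/after-sham test is named. What is missing is a comparison between the two conditions.
- A reader might infer that MSC will never be compared with sham. The list of contrasts is open-ended, the imaging ANOVA is unspecified, and the full protocol and SAP are not shown. The article supports only that no such test is stated.
- A reader might infer that the plan intends to call a non-significant result stabilisation, or to set a significant sham p-value against a non-significant MSC one. The text says neither. The stated analysis leaves room for both.

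The open details do not remove the fault. The article does not leave the efficacy test to another document: it fixes the pooled pairs, and it claims that the placebo effect is excluded.

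It is also fair to say that the article gives no schedule of clinical visits. Quality of life and imaging visits are timed from MSC, so a month-6 value before MSC in the delayed arm is not assured for those outcomes.

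**Conclusion.** The stated efficacy analysis is wrong for the secondary objective. The before/after-MSC test, alone or beside a separate before/after-sham test, cannot distinguish an MSC effect from progression or placebo response. The claims in the Abstract and Discussion about the sham control therefore have no stated test behind them.

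This follows from the text and the design, without any numerical assumption. The percentages are illustrations that depend on the assumed decline, normality and independence. The article supports the direction of the problem, not its exact size. The design itself is sound on this point, since it contains the randomised 6-month contrast that is needed.

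**What to change.** In the Statistics section, make the efficacy analysis the comparison of change from randomisation baseline to month 6, measured before the second procedure, between immediate MSC and immediate sham. Adjust for the baseline score (ANCOVA or its rank version) and report the estimate with a 95% CI. Keep the 20-pair before/after-MSC comparison as descriptive, and do not use sham given after MSC as the control.

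Apply this to outcomes that have a month-6, pre-MSC value in the delayed arm. The before/after-sham and before-MSC values that General considerations already requires should supply it for the variables tested there. For imaging and PDQ-8, use the comparison only if that pre-MSC assessment exists; otherwise report those outcomes descriptively. State also whether the total of 20 patients includes the 5 open-phase patients.

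For outcomes with the month-6 value, the cost is a change of wording, with no new patients. The downside is the wide interval and large detectable difference shown above. That is less flattering than 20 pairs, but the estimate rests on randomisation. The statements about excluding the placebo effect should then refer to this comparison.

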#### Safety data

A descriptive analysis of all AEs and ADRs will be provided.

The tabulations of laboratory data will be provided together with the normal ranges of the laboratory, highlighting any values that are out of range.

#### Motor function

A descriptive analysis of the course of the main endpoints will be provided:

–change in total, ADL, motor and part IV UPDRS score;

–change in Hoehn & Yahr stage;

–change in PSP rating scale (cognitive disturbances, bulbar functions, limb function, ocular motor function);

–change in SEADL;

–CGI score.

#### Multifactorial movement analysis

The data related to each of the four tests will be normalized and the mean of the values related to each variable recorded during the 8 walks will be calculated. The data before and after MSC therapy will be compared using Wilcoxon’s signed rank test for matched pairs, considering the patients before and after treatment as a pair (the results at each follow-up visit will be assessed separately). Moreover, the results obtained in PSP patients will be compared with those obtained in the group of age-matched healthy volunteers using the non-parametric Mann–Whitney U Test.

#### Neuropsychological assessments

A descriptive analysis of the course of the main endpoints (change in each of the test scores vs baseline will be provided).

#### Neuroimaging assessment

The main neuroimaging parameter will be:

–specific striatal uptake of the labeled ligand for SPECT analysis; this parameter measures the striatal density of dopamine transporters

–normalized labeled ligand subcortical and cortical uptake for PET analysis; this parameter measures normalized regional cerebral flow/glucose metabolism in the gray matter of the brain.

The analysis will be performed using ANOVA to assess changes in cerebral volume by SPM software. Significance will be set at p<0.01.

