### Neuroimaging

All patients perform a longitudinal neuroimaging assessment at baseline and 6, 12 and 18 months after MSC therapy, using striatal dopamine transporter Single Photon Emission Computed Tomography (SPECT) and Positron Emission Tomography (PET) using a tropanic tracer labeled with Iodine-123 (FP-CIT) for SPECT imaging and Iodine-124 (Beta-CIT) for PET/TC imaging. SPECT studies are carried after intravenous administration of 110-140 MBq of ^123^I-FP-CIT (Datscan®, GE-Health, Amersham, UK) performed 30–40 minutes after thyroid blockade (10–15 mg of Lugol solution per os) in all subjects. ^18^ F-fluorodeoxyglucose positron emission tomography (FDG-PET/TC) is performed 4–6 hours and 20–24 hours after intravenous injection of 18–30 MBq of ^124^I- Beta-CIT. All patients undergo ^18^ F-fluoro-2-deoxy-D-glucose positron emission tomography scanning (FDG-PET) at rest, after intravenous injection of 285 to 296 MBq.

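### The only stated imaging analysis tests cerebral volume, but both declared imaging parameters are tracer uptake, and the PET outcome is defined inconsistently

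*Protocol article*

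**What the plan says.** Under Neuroimaging assessment in the Statistics section, the protocol article lists two main parameters. The SPECT parameter is "specific striatal uptake of the labeled ligand for SPECT analysis; this parameter measures the striatal density of dopamine transporters". The PET parameter is normalized ligand uptake in cortical and subcortical regions, and the article adds that "this parameter measures normalized regional cerebral flow/glucose metabolism in the gray matter of the brain". The analysis is given in two sentences: "The analysis will be performed using ANOVA to assess changes in cerebral volume by SPM software" and "Significance will be set at p<0.01". Elsewhere the general level is 0.05: "P-values < 0,05 will be considered statistically significant".

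The Neuroimaging section of the methods describes the scans. SPECT uses an iodine-123 transporter ligand. PET is introduced under the same transporter heading with "Iodine-124 (Beta-CIT) for PET/TC imaging". A later sentence says that the FDG scan ("FDG-PET/TC) is performed 4–6 hours and 20–24 hours after intravenous injection of 18–30 MBq") follows an injection of iodine-124 Beta-CIT. The next sentence describes an FDG-PET scan with its own FDG injection. On timing, the section says: "All patients perform a longitudinal neuroimaging assessment at baseline and 6, 12 and 18 months after MSC therapy".

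**The concern.** The analysis sentence names a quantity that neither declared parameter measures. Stabilization or improvement in neuroimaging findings is part of the secondary objective, and the Discussion criticises earlier cell-therapy studies because their imaging did not focus on the damage seen in parkinsonism. Transporter uptake appears to be this trial's answer to that gap, yet the one sentence that says what will be tested leaves it out.

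The PET text adds a second ambiguity. Two tracers with different targets are planned, but only one PET parameter is defined. Where the analysed quantity is unclear, it can be settled after the scans have been seen. In a randomized phase of 20 patients with several imaging readouts, that freedom weakens any imaging result.

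**Working it through.** **1. Declared parameter against tested quantity**

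| Item | Where | Quantity |
|---|---|---|
| SPECT parameter | Neuroimaging assessment | striatal ligand uptake (transporter density) |
| PET parameter | Neuroimaging assessment | normalized regional uptake (flow or glucose metabolism) |
| ANOVA in SPM | Neuroimaging assessment | change in cerebral volume |
| Longitudinal scans | Neuroimaging | SPECT and PET only |
| MRI after infusion | Administration of MSCs | FLAIR and DWI, once the infusion is complete |
| MRI at entry | Table 1 | eligibility |

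No row supplies a longitudinal volume measurement. The tested quantity has neither a declared endpoint nor a scheduled acquisition.

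**2. PET tracers against PET outcomes**

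- Planned tracers: iodine-124 Beta-CIT (presented as transporter imaging) and FDG (glucose metabolism).
- Defined PET parameters: one, described as ligand uptake but interpreted as flow or glucose metabolism.
- Consequence: if the parameter means FDG, Beta-CIT PET has no outcome. If it means Beta-CIT, the interpretation does not fit the transporter role given to it in the methods.
- The sentence with the 4–6 and 20–24 hour acquisition times calls the scan FDG-PET but the injected tracer Beta-CIT. The FDG scan is then described again with a different injection. The two sentences need to be reconciled.

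**3. The p<0.01 threshold**

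This is a chosen level, so there is no derived figure to reproduce. The article does not say whether it is corrected, or whether it applies to voxels, clusters or regions. The number of tests m is not given, so all values of m below are assumptions.

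If 0.01 is uncorrected and applied to m independent regional tests, family-wise error = 1 − (1 − 0.01)^m:

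| m | Family-wise error |
|---|---|
| 1 | 0.010 |
| 5 | 0.049 |
| 6 | 0.059 |
| 10 | 0.096 |
| 20 | 0.182 |

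Up to five tests the error stays below 0.05.

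If 0.01 is uncorrected and applied voxel by voxel, the expected number of false-positive voxels under the null is 0.01 × m, with no independence assumption needed:

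- 0.01 × 20,000 = 200
- 0.01 × 150,000 = 1,500
- 0.01 × 200,000 = 2,000

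If 0.01 is already a corrected level, there is no inflation.

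**4. Scan times in the sham-first arm**

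The Study design section sets a delay of 6 months and a total duration of 18 months. Counting scans from MSC therapy, as the Neuroimaging section does:

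- Immediate MSC: study months 6, 12 and 18.
- Sham first: 6 + 6 = 12, 6 + 12 = 18 and 6 + 18 = 24.

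Read literally, the last sham-first scan falls 6 months after the study ends, and no month-6 scan is stated for that arm. Visits counted from study baseline would fit 18 months, but the article does not say that.

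**The case against.** The strongest reply is that the volume phrase is loose wording, perhaps for changes across the brain volume. The analysis sentence directly follows the two uptake parameters, and no volumetric scan is planned, so the investigators probably mean to analyse uptake. That is plausible, and it makes this a wording correction. It does not show that the endpoints would go unanalysed. But this is the only imaging analysis sentence in the article, and as written it names the wrong quantity. The tracer inconsistency cannot be explained in the same way.

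A reader might go further and infer that a whole-brain map at an uncorrected p<0.01 would almost certainly show positive regions for an inert product. The article does not support that. It never says voxel-wise, whole-brain or uncorrected. SPM makes voxel-wise mapping a reasonable guess, not a stated plan. The correction method and the ANOVA factors are details that a condensed article may leave to the full protocol or analysis plan, so their absence is not an error. The stated level is also stricter than the general 0.05, and the first declared parameter concerns the striatum, which could mean only a few regional tests.

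It is also fair to say that the primary objective is safety, that imaging is one of three secondary components, and that the Discussion itself says no validated biomarker exists for following a neuroprotective effect. This limits the severity.

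**Conclusion.** Two errors stand on the face of the article. The stated imaging analysis tests cerebral volume although both declared parameters are tracer uptake and no volumetric imaging is scheduled. The PET outcome merges two tracers into one parameter and times an FDG scan from a Beta-CIT injection, leaving it unclear what outcome Beta-CIT PET has. Neither conclusion rests on an assumed number.

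The false-positive issue is conditional. It is large (about 1% of voxels, or 1,500 to 2,000 of an assumed 150,000 to 200,000) only if the threshold is uncorrected and voxel-wise. There is no excess over 0.05 if the threshold is corrected or covers at most about five regional tests.

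Severity is moderate: the imaging analysis needs correcting before the data are analysed, but it serves a secondary objective and the primary safety assessment does not depend on it.

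**What to change.** - In Neuroimaging assessment, replace cerebral volume with change in tracer uptake, naming the SPECT and PET parameters already listed.
- Define Beta-CIT PET and FDG-PET as separate outcomes, each with its own parameter and interpretation.
- Reconcile the Neuroimaging and Neuroimaging assessment sections so that each injection and acquisition time is attached to the tracer it belongs to. The sponsor must state which that is.
- State what p<0.01 applies to. If it was meant as an uncorrected voxel-wise threshold, use a family-wise-error-corrected level instead. If it is corrected, or applies to a few named regions, say so.
- Before planning any month-6 comparison of immediate MSC with immediate sham on imaging, reconcile the scan times counted from MSC therapy with the 18-month study duration, and confirm whether the sham-first arm is scanned at month 6. Until then it cannot be assumed that this comparison needs no extra scans.

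The cost of the first four items is wording. If a correction is applied, fewer regions will reach significance.
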